**Methods:**

A total of 4,000 adult participants meeting International Classification of Sleep Disorders, 3rd Edition (ICSD-3) criteria for insomnia disorder will be recruited from community or clinical settings. Eligible participants will be invited to complete the multi-dimensional assessments via a digital platform, including a structured interview, questionnaires, cognitive tasks, sleep-activity diary, physiological characteristics, and ecology momentary assessments, as well as 7-day physical activity and sleep tracking using wearable devices. All participants will be followed up at 6 and 12 months. The primary outcome is the identification of multi-modal subtypes of insomnia disorder and their correlates. Secondary outcomes include the longitudinal trajectories of these subtypes, associated risk factors, and mental health outcomes.

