**Fig. 2 Fig2:**
[figure not shown]
Geographic distribution of the 33 collaborative study sites across China

All individuals participating in the study are permitted to continue their ongoing treatments and medications, which will be recorded and documented throughout the research. In addition, electronic Cognitive Behavioral Therapy for Insomnia (e-CBTI), a routine fee-based clinical service delivered via a smartphone application, was optionally accessible to participants; for those who opted in, the study team covered the service fee without modifying the treatment content or delivery.

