#### Multimodal data integration

Questionnaire, EMA, wearable, and cognitive task data will be integrated using a unified preprocessing and clustering framework. Within each modality, features are selected to capture distinct aspects of insomnia-related functioning, such as mental disorders and symptoms, cognition, objective sleep parameters, and demographic characteristics. Variables with low variance or > 30% missingness will be excluded. To eliminate the influence of differing scales and units across features, continuous variables are standardized using Z-score normalization.

To address multicollinearity and redundant information, we construct a pairwise correlation matrix and visualized it with a heatmap to identify highly correlated feature pairs (|r| > 0.8). Two mainstream strategies will be considered: (1) Feature selection using Lasso regression with 10-fold cross-validation to retain the most informative variables while shrinking redundant coefficients to zero; and (2) Feature dimensionality reduction using principal component analysis (PCA), which transforms correlated variables into orthogonal principal components while preserving most of the data variance. After preliminary testing, PCA is selected as the final approach based on its superior performance in preserving global data structure and compatibility with K-means clustering’s independence assumptions. Components explaining > 85% of the cumulative variance will be retained for subsequent analyses.

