#### Subtyping procedures

The standardized features from each modality are concatenated into a single feature matrix, and variance normalization is applied to balance the contribution of different modalities in subsequent analyses [75, 76]. PCA was further applied for dimensionality reduction, followed by K-means clustering to identify distinct insomnia subtypes.

The optimal number of clusters (k) was determined using the elbow, silhouette, and Gap statistics. To assess clustering robustness, bootstrap resampling (1,000 iterations) and consensus clustering will be performed [77]. Cluster characteristics will be summarized using standardized centroid differences and key feature importance, providing interpretable profiles of each subtype. Sensitivity analyses will be conducted to compare equal-weight versus data-driven weighting schemes to evaluate the robustness of the clustering results. The defining features of each cluster are examined to understand the underlying pathophysiological mechanisms and clinical presentations.

Aggregated features obtained from Zhiyoumian and wearable devices as well as their changes from baseline, will be incorporated into the statistical analyses. Machine learning techniques will be applied to build predictive models evaluating the stability and clinical predictive value of these subtypes.

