## Strengths and limitations

The DIMOSI study has several notable strengths. First, the current study is a prospective cohort with a nationally representative large-scale sample recruited from both the community and clinical settings. All participants met diagnostic criteria through face-to-face clinical interviews based on ICSD-3 standards. This provides a sufficient number of representative participants, enabling the exploration of systematic subtypes and the assessment of their stability and predictive value. Second, the study employs comprehensive assessments, including traditional subjective measures, cognitive function evaluations, and objective measures of sleep and physical activity. Third, the integrated digital platform broadens the application scenarios in terms of time and location, making assessments of insomnia disorder more convenient and improving participant compliance.

However, several limitations of this study should be acknowledged. First, some participants were using sleep medications at baseline, which may have resulted in lower ISI scores at enrollment. We recorded these conditions and used statistical techniques to control for these factors. Second, considering that the main aim of this study is to analyze the subtype analysis of insomnia disorders rather than biological markers, biological sample testing was not included [90]. Third, while the comprehensive application of digital technology has conferred efficiency and high data quality, it may exclude some patients who are unable to use electronic devices. Finally, the current study uses convenience sampling, which may have introduced selection bias and limited generalizability, but we mitigated this via screening logs and community-clinic sensitivity analyses.

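### Sleep medication is said to be controlled for, but no stated step of the clustering that produces the primary outcome accounts for it

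*Protocol article*

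**What the plan says.** In Strengths and limitations, the first limitation listed is that "some participants were using sleep medications at baseline, which may have resulted in lower ISI scores at enrollment". The answer given is: "We recorded these conditions and used statistical techniques to control for these factors". No technique, variable or model is named.

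The Study population section (text after Fig. 2) says that participants are "permitted to continue their ongoing treatments and medications, which will be recorded and documented throughout the research". The data needed to account for medication are therefore collected.

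The abstract defines the target: "The primary outcome is the identification of multi-modal subtypes of insomnia disorder and their correlates". Two sections describe how the subtypes are made.

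- **Multimodal data integration:** "features are selected to capture distinct aspects of insomnia-related functioning, such as mental disorders and symptoms, cognition, objective sleep parameters, and demographic characteristics"; then "continuous variables are standardized using Z-score normalization"; then "Components explaining > 85% of the cumulative variance will be retained for subsequent analyses".
- **Subtyping procedures:** "PCA was further applied for dimensionality reduction, followed by K-means clustering to identify distinct insomnia subtypes". The number of clusters, 1,000 bootstrap resamples, consensus clustering and a comparison of weighting schemes follow.

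**The concern.** The article treats medication as a known disturbance of a baseline measure and tells the reader that it has been dealt with. The analysis carrying the primary outcome, as described, does not deal with it. K-means has no covariate term, so medication can be accounted for only before the clustering (by restricting the sample or adjusting the features) or by a repeat analysis beside it. Neither is stated.

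If medication shifts several baseline features together, a severely ill treated patient and a milder untreated patient can look alike and share a subtype. The subtypes are meant to show natural trajectories and to predict treatment response. A subtype defined partly by who was already treated would carry part of a treatment effect in its prognosis.

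**Working it through.** **1. Each stated step, checked for medication.**

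| Step | Accounts for medication? |
|---|---|
| Feature choice within modality | Not named; the list is open-ended |
| Low-variance and >30% missingness filters | No |
| Z-score | No; no standardisation within medication group is stated |
| Correlation check, \|r\| > 0.8 | No |
| PCA to >85% of variance | No |
| Modality weighting | No |
| K-means; elbow, silhouette and Gap | No |
| 1,000 bootstraps, consensus clustering | No; a split driven by medication could reproduce well |
| Sensitivity analysis | Weighting schemes only |

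Elsewhere, Strengths and limitations names community-clinic sensitivity analyses. These compare recruitment settings, and Table 2 gives no medication use by setting. Longitudinal modeling names no medication covariate.

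**2. Why later adjustment does not repair the labels.** Write an observed feature as X = X0 + δM, with M = 1 for medication users. The label is C = f(X). A follow-up model with C and M as predictors adjusts the coefficient of C, but who belongs to each C was settled from X, with δM inside it.

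**3. Size on the ISI alone.** The document gives an ISI SD of 5.8. It gives no share of users p and no effect Δ, so both are assumed. The share of ISI variance is p(1−p)(Δ/5.8)².

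- p = 0.3, Δ = 2: 0.21 × 0.345² = 0.025
- p = 0.4, Δ = 3: 0.24 × 0.517² = 0.064
- p = 0.5, Δ = 4: 0.25 × 0.690² = 0.119

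This is about 2.5% to 12% of the variance of one feature among the 40–80 planned.

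**4. Size on the clusters: a simulation.** The plan states no figure for medication to reproduce. Its sample size does reproduce (80 variables × 50 = 4,000) and was used here. Settings: n = 4,000; 60 correlated features; whole-sample Z-score; PCA to 85%; K-means with k = 3; four seeds per setting. Assumed values: 20–60% users, and a shift of 0.3–0.8 SD on 30% or 60% of features. The measure is Cramér's V between cluster and medication (0 = unrelated, 1 = identical).

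| Shift | V, no true subtypes | V, strong true subtypes |
|---|---|---|
| 0.3 SD | 0.04–0.08 | 0.02–0.03 |
| 0.5 SD | 0.08–0.30 | 0.02–0.04 |
| 0.8 SD | 0.24–0.95 | 0.03–0.04, but 0.25 and 0.44 in two settings |

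Example without true subtypes: with 40% users and 0.5 SD on 60% of features, the share of users by cluster ran from 28% to 61%. With strong true subtypes, 16 of 18 settings stayed at V ≤ 0.04. The two exceptions had 0.8 SD on 60% of features with 40% or 60% users. That shift exceeds the 0.34–0.69 SD assumed for the ISI in step 3. Centring features within medication group first gave V of 0.01–0.02 in every setting.

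**The case against.** The strongest reply is that this is a condensed article. The full protocol and analysis plan are not shown and may specify an adjustment. The sentence on control mentions ISI scores, not clustering, and could refer to the regression and mixed models, where covariates are ordinary. The feature list is open, methods may be changed to suit the data, and the community-clinic analyses show that the article names some analyses outside its statistical section.

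Much of this stands. A reader might infer that the claimed control does not exist, or that the sentence is false. The document does not support that; it supports only that no such step is stated here. A reader might also take it that medication does lower the ISI, or that it will dominate a leading principal component. The article says only that it may have lowered scores, and the loading is not shown.

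What remains is more than missing detail. The article sets out the pipeline down to correlation thresholds and bootstrap counts, and offers control as its answer to its first-listed limitation. If that control means only the follow-up models, the primary outcome is still left without it. Entering medication as a clustering feature would not control for it either; it would pull the clusters towards medication groups.

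**Conclusion.** The point holds in limited form. Control for medication is asserted, while the described analysis of the primary outcome has no step that provides it, and adjustment of later models would come too late to change the labels. Subtypes could therefore partly reflect current treatment.

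How far they do so cannot be derived from the document. Under the assumed values the association between cluster and medication ranges from negligible to near complete when no true subtypes exist, and is small in nearly all settings when true subtypes are strong. It would go too far to conclude that the subtypes will be medication groups. The finding rests on the text alone; the simulation only shows that the risk can be material. A change should be made, because the data are already recorded and the check is cheap.

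**What to change.** 1. In Subtyping procedures, add a sensitivity analysis: repeat the whole pipeline, from standardisation onwards, in participants not using sleep medication at baseline. Report agreement with the main labels in those same participants (for example the adjusted Rand index) and the share of medication users in each main subtype.
2. In Longitudinal modeling, name baseline sleep medication as a covariate in the follow-up models.
3. In Strengths and limitations, limit the sentence on control to the analyses where adjustment is actually made, and name them.
4. Optionally, as a secondary check only, repeat the clustering on features residualised for medication.

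The cost is one further clustering run (two with the optional check), one descriptive table and a text edit. No new data are needed and no participant's treatment is affected. There are real downsides. The non-user subset is smaller, so its clusters are less precise, and it may be selectively milder, so disagreement with the main labels need not mean a medication effect. Residualising may remove genuine severity differences because medication use can track severity, which is why it should not replace the main analysis.

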## Conclusions

The DIMOSI study is a national multicentre prospective cohort study utilizing an integrated digital assessment platform, conducted among adult patients with insomnia disorder. This study provides a unique opportunity to explore the subtypes of insomnia disorder, which hold predictive value for the clinical trajectories and treatment responses.

## Data Availability

The datasets generated and analysed during the current study are not publicly available due to participant privacy and institutional regulations, but are available from the corresponding author on reasonable request and with appropriate institutional approval.

## Abbreviations

DIMOSI: The Digital Multi-modal Approaches to Subtyping Insomnia Disorder
DIS: Difficulty initiating sleep
DMS: Difficulty maintaining sleep
EPV: Estimated events per variable
e-CBTI: Electronic Cognitive Behavioral Therapy for Insomnia
EMA: Ecological momentary assessment
ICSD-3: The International Classification of Sleep Disorders, Third Edition
DSM-5: The Diagnostic and Statistical Manual of Mental Disorders, Fifth Edition
